### Sample size determination

The required sample size was calculated according to one of the primary outcome measures, which is the difference in LUS scores at T1 between assignment groups, based on preliminary results (alpha = 0.05, power (1-ß err prob) = 80%, effect size f = 1.6) (unpublished data).

Estimating a conservative attrition rate of 15%, our sample size will include 150 participants over 30 months.

### Randomization/blinding

After enrolment, participants will be randomly assigned to LUS-monitored or standard care group by the use of block-generator software. Both the clinicians who will perform and score LUS, and the patients’ family will be blinded to randomization.

The child neurologist and the SLP will be informed of the result of LUS only in the LUS-m group and will include that result to impact on feeding care (postural- hygiene care adaptation, thickening fluids or drugs available for GERD). LUS results in the SC-m group will be available only at the time of data analyses.

### Adverse events

Any adverse event or unintended effect associated with the intervention will be reported and reviewed by researchers. In case of detection of LUS pulmonary abnormalities that will be considered a medical emergency which compromises a participant’s safety, unblinding will be permissible. The child neurologist will be informed of the unlikely result and will inform the family for appropriate therapy.

### LUS procedure/Equipment

The intervention is a LUS-monitored (before and after) feeding trial (the “after” evaluation will be within 15 min the end of the feeding procedure). A further LUS evaluation will be performed at a distance of 3 h, before the next meal to check for resolution of eventual after-meal abnormalities. All meals will be monitored by pulse-oximetry and video recorded.

Lung ultrasound exam will be performed based on a previously described scanning scheme in children [25], as indicated in Fig. 2. Commercially available portable machines with a linear probe (9–12 MHz) with specific setting for infants will be used (Lumify, Philips Medical Systems, Andover, MA, USA). Acquired images and movies will be saved in both groups but only available for final analyses in the SC-m group. In detail, the thorax will be divided into 3 major scanning areas (anterior, lateral, and posterior) divided by the parasternal, anterior axillary, and posterior axillary anatomical lines on both the right end the left hemithorax. A deaeration score will be used to classify each LUS exams, taking into account the following signs in each scanning area: the number of B-lines; the appearance of the pleural line; presence of C-lines; presence of small peripheral sub-pleural consolidations; presence of large consolidations; presence of pleural effusion. A deareation score will be calculated before and after the meal, so when the after-meal score will be different from pre-meal score (more than 10%), an intervention will be assigned to modify feeding performance and reported as medical, postural or food consistencies adaptation in the experimental group.

**Fig. 2 Fig2:**
[figure not shown]
LUS scanning scheme. Ten scanning areas are identified. ASR: anterior superior right; AIR: anterior inferior right; ASL: anterior superior left; AIL: anterior inferior left; LR. Lateral Right; LL: Lateral left; PSR: Posterior Superior Right; PIR: Posterior Inferior Right; PSL: Posterior Superior Left; PIL: Posterior Inferior Left

### Assessments

Infants will be assessed for outcomes according to the timeline. At T0, neurological information will be collected by using the Hammersmith Infant Neurological Examination (HINE) [26]; Alberta Infant Motor Scale (AIMS, [27]), GMFCS E&R [28]. The clinical measures used are standardized and validated for use across a wide age range.

Clinical primary outcomes will be rate of pulmonary illness (including pneumonia, wheezing, chronic cough, and apnea rate) and performance at growth curves (according to WHO growth standards, eventually age-corrected because of premature birth, or according to specific syndrome growth standards as recommended by ESPGHAN [9]. Between T0 and T2, parents will be asked to fill a detailed respiratory infection-diary for respiratory illness rate calculation (information collected at both T1 and T2). We will consider the exact, separate number of upper and lower airways infection and detect patients suffering from RRI (Recurrent Respiratory Infections), according to the most recent definition, i.e. i) 6 or more airways infection/year (at least 1 pneumonia, even severe), or ii) 2 pneumoniae even not severe but radiologically confirmed [29].

Primary outcome measure will include LUS score at T1. We assume that a better baseline detection of aspiration will result in better management with a reduction of pulmonary abnormalities detected by LUS at primary endpoint. Secondary outcomes collected at T1 will include chronic pain assessment (parents-report measures, behavioral measures including the Non-communicating Children’s Pain Checklist, and physiological measures) [30] and parents’ stress by a parent stress questionnaire (Parenting Stress Index PSI) [31]. At T0 and T2 laboratory exams will be performed to evaluate general and nutritional status (blood cells count, reticulocytes count, ferritin, total serum protein electrophoresis, prealbumin, transferrin, TSH, FT3, FT4, sodium, potassium, calcium, phosphorus, folates, vitamin B12, 25-OH-vitamin D, C-reactive protein, erythrocyte sedimentation rate, Insulin-like Growth Factor I) and quantitative ultrasound (QUS) also, in order to quantify bone mineralization.

VFSS and FEES data will be collected when performed according to multidisciplinary clinical indications, compared in frequency of execution between groups, and their results will be compared to LUS findings.

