Oral fluid, food or refluxed gastric contents can be aspirated into the lungs, apparently, by choking or coughing, or silently. In order to directly or indirectly diagnose aspiration in dysphagia and GERD, video-fluoroscopic swallowing study (VFSS) and fiber-optic endoscopic examination of swallowing (FEES) are options, however they focus on a single study, thus clinical diagnosis is seldom made despite a normal result and, due to radiation exposure, invasiveness and costs, they are poorly reproducible in the same patient [11–13]. Furthermore, rheological and material property parameters among the barium-impregnated liquids and the thickened and unthicken infant formula are different, thus biasing the interpretation of the radiological results and consequent clinical recommendations [13, 14]. Finally, only clinical feeding evaluation and empirical trials are applied to provide support to the management of feeding difficulties related to dysphagia or GERD, and no standardized feeding or behavioral measure exists at any age to assess aspiration risk and support the indication to perform VFSS or FEES.

The picture is further complicated at young ages, as recently the concept of ‘early diagnosis’ has emerged for cerebral palsy and a variety of neurological disorders [15]. Indeed, most studies focusing on dysphagia and GERD in neurologically impaired children refer to ages older than 1 year. In the few studies investigating dysphagia in infants younger than 1 year by using VFSS, aspiration was present in 50% of infants with suspected dysphagia and up to 90% of them had silent aspiration [16]. This indicates that many infants who are not clinically suspected of having dysphagia or GERD may have silent aspiration, therefore a monitoring would be recommended in infants with higher aspiration risk, starting early from the first days of life. This would lead to earlier diagnosis, clinical management ad tailored habilitation and nutritional strategies to improve outcome and limit short-term and long-term complications [17].

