**Fig. 1 Fig1:**
[figure not shown]
Schedule of study enrolment, interventions, and assessments

The main aim of the presented trial is to explore the effectiveness of the use of LUS for monitoring pulmonary abnormalities related to aspiration during feeding in neurologically impaired infants, by comparing integrated LUS-monitored management of dysphagia to standard care in terms of medical/neurological/behavioral status, chronic pain/discomfort and stress for caregivers.

Specific hypotheses to be tested are:Infants receiving LUS-monitored management will have lower rate of pulmonary illness and better growth curves, corresponding to less after-meal LUS abnormalities over time, compared to infants receiving standard care. They will also reduce the need for invasive diagnostic (VFSS/FEES) over time.Infants receiving LUS-monitored management will have better results at blood sample and bone metabolism, lower pain indices and less stressful interaction with caregivers.

We also hypothesized that diagnostic benefits of LUS-monitored management will contribute to better neurological outcome.

Further aims also include the comparison between LUS and VFSS/FEES in the detection of feeding-related silent or apparent aspiration and to estimate aspiration entity by cut-off values for the diagnosis of clinically significant silent or overt aspiration, responsiveness of LUS monitoring to medical, postural or food consistencies adaptation, and their relationship with standardized clinical feeding evaluation and medical/behavioral/neurological measures. Moreover, we will explore the impact of brain abnormalities detected by brain MRI on LUS findings severity.

We will finally establish risk categories for unsafe swallowing disorders and potential clinical recommendations for early management.

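### The claim of reduced need for VFSS/FEES rests on a between-arm count of tests, which measures use, not need

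*Protocol article*

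**What the plan says.** The specific hypotheses in Methods state of infants in the LUS-m arm: "They will also reduce the need for invasive diagnostic (VFSS/FEES) over time". The Background ends with the same expectation, and the Discussion looks forward to fewer X-ray examinations.

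The Assessments section fixes how this is examined. Who is tested is left to clinical judgement: "VFSS and FEES data will be collected when performed according to multidisciplinary clinical indications". The tests are then "compared in frequency of execution between groups, and their results will be compared to LUS findings". The between-arm comparison is therefore of frequency, and the test results are set against LUS. The aims in Methods treat the results in the same way: "Further aims also include the comparison between LUS and VFSS/FEES in the detection of feeding-related silent or apparent aspiration". Neither Assessments nor Statistical analysis compares test results between arms.

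Two other statements matter. Under Randomization/blinding, "The child neurologist and the SLP will be informed of the result of LUS only in the LUS-m group". And the Background gives as a gap in current practice that "no standardized feeding or behavioral measure exists at any age to assess aspiration risk and support the indication to perform VFSS or FEES", adding that "many infants who are not clinically suspected of having dysphagia or GERD may have silent aspiration".

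**The concern.** Need and use are different quantities. Use is how many tests were done. Need is how many had to be done for children to be properly diagnosed and managed. A lower count in LUS-m has at least three explanations:

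- LUS spared children who would have tested negative.
- LUS findings led directly to a change in feeding care, so the test became redundant.
- A reassuring LUS stopped the referral of children who do aspirate.

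The first two support the hypothesis and the third contradicts it. A higher count is also ambiguous. The article expects benefit through better detection of aspiration that is often silent, and better detection could send more children to VFSS/FEES. Read against the hypothesis as worded, that would count against LUS.

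At stake is one stated conclusion of the trial, that LUS lowers the need for invasive testing. The frequency comparison cannot carry that conclusion alone.

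**Working it through.** The article gives no expected VFSS/FEES rate or yield, so there is no figure to reproduce. The check is whether the stated comparison can tell the explanations apart. All testing rates below are assumptions.

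**Inputs from the article.** 63 per arm (Participants); 150 in total, so 75 per arm (Sample size determination); and, from the Background, "aspiration was present in 50% of infants with suspected dysphagia and up to 90% of them had silent aspiration". The 50% comes from infants under 1 year with suspected dysphagia. The trial enrols children aged 0 to 6 years, some without suspected dysphagia, so applying 50% to this sample is itself an assumption.

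**Step 1: same count, different meaning.** Assume 30 of 75 children tested in standard care (SC-m) and 15 of 75 in LUS-m, counting children and not tests. Fisher's exact test, two-sided, gives p = 0.012. With 63 per arm, 25 against 13 tested gives p = 0.032.

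Positive children = children tested × yield:

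- SC-m: 30 × 0.5 = 15.
- LUS-m, yield 100%: 15 × 1.0 = 15.
- LUS-m, yield still 50%: 15 × 0.5 = 7.5, that is 7 or 8.

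The p-value is identical in both LUS-m cases, necessarily so, because yield does not enter the comparison.

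**Step 2: scenarios with 63 per arm.** Assume half aspirate and that a test confirms aspiration when it is present. Let a and b be the probabilities of testing an aspirator and a non-aspirator. Then tested = 63 × (a + b)/2, positive = 63 × a/2, only negative = 63 × b/2, and aspirators not confirmed by VFSS/FEES = 63 × (1 − a)/2.

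| Scenario | a, b | Tested | Positive | Only negative | Not confirmed |
|---|---|---|---|---|---|
| SC-m | 0.5, 0.3 | 25.2 (40%) | 15.8 | 9.5 | 15.8 |
| LUS-m A: fewer referrals overall | 0.2, 0.2 | 12.6 (20%) | 6.3 | 6.3 | 25.2 |
| LUS-m B: only non-aspirators spared | 0.5, 0 | 15.8 (25%) | 15.8 | 0 | 15.8 |
| LUS-m C: better case-finding | 0.9, 0.1 | 31.5 (50%) | 28.4 | 3.2 | 3.2 |

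On frequency, A and B look alike (20% and 25% against 40%), and C looks like the opposite of the hypothesis. Positive and only-negative children per randomised child separate all three.

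**Step 3: what these counts still cannot show.** Row A fits two opposite stories: false reassurance, or aspirators recognised on LUS and managed without a test. LUS procedure/Equipment provides for the second, since a change in score of more than 10% after the meal leads to an adaptation in the experimental arm without requiring VFSS/FEES. Not confirmed is therefore not the same as missed. Separating the two needs the number of LUS-m children with an adaptation but no test, and the clinical outcomes.

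**Step 4: could an ambiguous fall reach significance?** For 40% against 20% tested, power is about 69% with 63 per arm and 77% with 75. A fall of this size could well give p < 0.05, whatever its cause.

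**Step 5: does comparing results with LUS help?** Only partly. It covers tested children only, and in LUS-m the LUS result can influence who is tested. Aspirators who are never referred do not appear in it.

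**The case against.** The case against is substantial, and much of it stands.

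- **Frequency is a proper measure of burden.** If the aim is fewer invasive or radiating procedures, the number done measures it directly. This stands, and is why the count should stay, reported as use.
- **Fewer positive tests need not mean missed aspiration.** A reader might infer from Step 1 that about half the aspirators in LUS-m would be missed. The documents do not support that, because LUS results feed directly into feeding care in that arm. For the same reason, a rule that positive tests must not fall could reject a true success.
- **A safety check largely exists.** Pulmonary illness, growth and LUS score are primary outcomes. Airway infections are counted separately for upper and lower airways, and LUS is recorded in both arms, so untested children are followed too. A reader might infer that harm from false reassurance would go unseen; these outcomes give it several routes to appear. The article does not say, however, that they will be used to interpret the VFSS/FEES count.
- **The measure is peripheral.** VFSS/FEES frequency is neither a primary nor a named secondary outcome. This limits the weight of the point. It does not remove it, because reduced need is part of a stated hypothesis.
- **The full protocol or analysis plan may tabulate results by arm.** It may. But the article does not leave the between-arm comparison open; it names frequency.
- **The numbers are constructed.** They are. They show that the comparison cannot discriminate, not how large any error will be.

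**Conclusion.** The point holds for the reduced-need conclusion only. The article claims a reduction in need and specifies a between-arm comparison of use. That comparison cannot distinguish avoided unnecessary tests, substitution by LUS-guided care and non-referral of aspirators, and it would set better case-finding against the hypothesis. This follows from the definition of the measure and does not depend on the assumed rates.

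The size of any misreading cannot be estimated, because the article gives no VFSS/FEES rates or yields. The illustration (p = 0.012 for 15 against 30 of 75, with 15 or with 7 to 8 positives behind it) rests on assumed testing rates and on a 50% figure from a younger, more selected group.

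The point does not show that LUS leaves aspiration undetected, nor that the primary comparisons are affected. It is a moderate matter: an inexpensive change that decides what the trial may say on one stated hypothesis.

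**What to change.** In Assessments, replace the bare frequency comparison with the following, by arm, per randomised child and with confidence intervals:

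- (a) children with any VFSS/FEES;
- (b) children with any positive VFSS/FEES;
- (c) children tested with only negative results;
- for LUS-m, also children with a LUS-triggered feeding adaptation but no VFSS/FEES.

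State that frequency will be interpreted together with these counts and with the between-arm comparisons of lower-airway illness and LUS score. Conclude reduced need only when fewer tests come without worse results on those outcomes. Otherwise report reduced use, as a descriptive process measure. Do not require that positive tests must not fall.

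Cost: analysis wording only. The test results, adaptations, infection diary and LUS scores are already to be collected, and no clinical management changes. The counts in (b) and (c) will be small, their intervals wide, and the claim harder to make.

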### Statistical analysis

Statistical analyses will be performed by using a statistical software (Statistical Package for Social Sciences, SPSS). Descriptive statistics and baseline between group differences will be explored. Statistical significance will be considered at *p* < 0.05. Post-hoc adjustment will be applied for multiple comparisons. Changes in LUS-score, growth and pulmonary illness rates at the primary endpoint (T1) will be calculated to assess the short-term effects of LUS-management versus standard care. Secondary outcome measures will be calculated at T1 and T2. Covariates such as type of neurological impairment, type/severity of brain lesion and age, will be included in the analyses. Multivariate statistics will be finally performed. Data imputation will be considered according to characteristics and relationship of missing variables.

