### Participants

A minimum sample size of 126 subjects was determined (63 each group). Newborn and infants will be recruited by the child neurologist and the speech and language pathologist (SLP) from the Infant Neurology Section of academic hospital IRCCS Stella Maris Foundation in Pisa, Italy.

Subjects will be included in the study if: i) they have, or they are at risk for, cerebral palsy [15] or have abnormal muscular tone at any age between 0–6 years of life due disorders other than cerebral palsy; or ii) motor developmental delay assessed by a quantitative scale for infants and young children development (< 5 sd according to age); or iii) in absence of the previous clinical indices, if there is the suspicion of GERD or dysphagia based on clinical symptoms; iv) a brain MRI acquisition done before or programmed prior the end of the study period as part of their diagnostic procedure. Subjects will be excluded in presence of primary chronic lung diseases.

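### Growth, a clinical primary outcome, is to be analysed as change at T1 and the T0 value is not named as a covariate; adjusting for it would give a modest, free gain in precision

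*Protocol article*

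**What the plan says.** Under Assessments, the article lists growth, referenced to WHO or syndrome-specific growth standards, among the clinical primary outcomes, together with pulmonary illness rate. The LUS score at T1 is also primary.

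Under Statistical analysis, the form of the T1 comparison is change: "Changes in LUS-score, growth and pulmonary illness rates at the primary endpoint (T1) will be calculated to assess the short-term effects". The covariates are then described: "Covariates such as type of neurological impairment, type/severity of brain lesion and age, will be included in the analyses". No T0 value of any outcome is named. The same section says that baseline differences between groups will be explored, but attaches no adjustment rule to this.

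For the laboratory measures and quantitative bone ultrasound, Assessments gives the timing: "At T0 and T2 laboratory exams will be performed to evaluate general and nutritional status", with bone ultrasound in the same sentence. Statistical analysis says only that secondary outcomes will be calculated at T1 and T2. It does not say whether these are compared as change or as final value.

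**The concern.** A change score subtracts the whole of the T0 value, as if a child's T0 standing carried over to T1 one for one. When the T0-T1 correlation is below 1, that is too much. Two things follow.

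- **Precision.** The comparison carries more variance than one that lets the data set the weight given to T0.
- **Chance imbalance.** If one arm happens to start lower on growth, regression to the mean is expected to lift it somewhat by T1. The change score counts part of that rise as a treatment effect.

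Growth is a primary outcome and three months is a short interval, so the between-arm difference may well be small. The T0 growth value must be recorded for change to be computed at all. Leaving it out of the model therefore gives up information the trial already holds. The randomisation described is in blocks of 4 with no stratification mentioned, so nothing stated in the article balances T0 growth by design.

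**Working it through.** **The plan's own figure.** There is none for growth. The sample size rests on another outcome, "which is the difference in LUS scores at T1 between assignment groups", with "alpha = 0.05, power (1-ß err prob) = 80%, effect size f = 1.6". The printed effect size does not lead to 63 per arm: read as f = 1.6 (d = 3.2) it gives 2 per arm, and read as d = 1.6 it gives 7. A standardised difference of 0.50 gives 63. That is a separate matter and nothing below depends on it. Only the arm size is taken from it: "A minimum sample size of 126 subjects was determined (63 each group".

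**Inputs.**
- n = 63 per arm (Participants).
- Alpha 0.05 (Sample size determination), taken as two-sided because the article does not say.
- T0-T1 correlation r: not given, so assumed and shown over a range.
- Equal SD at T0 and T1, and growth expressed as a z-score: assumed. With other covariates in the model, r means the correlation that remains after them.

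**Variance per child, in units of the outcome variance.**
- Change score: 2(1-r).
- ANCOVA with the T0 value: 1-r² = (1-r)(1+r).
- Ratio, ANCOVA to change: (1+r)/2, which is below 1 for every r < 1.

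**Power.** Take the difference that the change score detects with 80% power, δ = (1.960 + 0.842) × √(2 × 2(1-r)/63). Power after adjustment is Φ(2.802/√((1+r)/2) - 1.960). At r = 0.8, for example, 2.802/√0.90 = 2.953, less 1.960 is 0.993, and Φ(0.993) = 0.84.

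| r (assumed) | Change variance | ANCOVA variance | Ratio | Detectable difference, change (SD) | Detectable difference, ANCOVA (SD) | Power instead of 80% |
|---|---|---|---|---|---|---|
| 0.5 | 1.00 | 0.75 | 0.75 | 0.499 | 0.432 | 90% |
| 0.7 | 0.60 | 0.51 | 0.85 | 0.387 | 0.356 | 86% |
| 0.8 | 0.40 | 0.36 | 0.90 | 0.316 | 0.300 | 84% |
| 0.9 | 0.20 | 0.19 | 0.95 | 0.223 | 0.218 | 82% |
| 0.95 | 0.10 | 0.098 | 0.975 | 0.158 | 0.156 | 81% |

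In numbers of children, (1 - ratio) × 126 is about 19 at r = 0.7, 13 at 0.8 and 6 at 0.9.

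**Chance imbalance.** The T0 mean difference between arms has SD √(2/63) = 0.178 of the outcome SD, with a 95% range of about ±1.96 × 0.178 = ±0.35. Given a T0 difference D, the expected T1 difference is the treatment effect + rD. Subtracting D leaves the treatment effect - (1-r)D. For D = 0.2 SD, not much above one SD of the chance difference, the residual is 0.06, 0.04, 0.02 and 0.01 SD at r = 0.7, 0.8, 0.9 and 0.95. It runs against the direction of the imbalance.

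**Laboratory and bone values at T2.** The saving depends on a choice the article does not state. If final T2 values are compared, T0 adjustment cuts the variance by r² (25% at r = 0.5, 49% at 0.7). If change is compared, it cuts it by (1-r)/2 (25% at 0.5, 15% at 0.7). At r = 0.7 the two readings differ threefold, so no single figure can be attached.

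**The case against.** The strongest reply is that nothing has been excluded. The covariate list is introduced as a set of examples, no model is named, and this is a condensed article whose full protocol and analysis plan may contain T0 adjustment. Calculating change is also compatible with it: regressing change on arm and T0 value gives the same treatment estimate as ANCOVA on the T1 value. This stands as a limit on the point. A reader might infer that the plan rules out baseline adjustment, and the text does not show that. What remains is that the article does state the form of the analysis and does choose which covariates to name. Followed as written, that combination is the less precise one.

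Two other stronger readings also fail. A reader might infer that chance imbalance in T0 growth is left untouched. It is not, because change already subtracts each child's T0 value; what is left is the smaller over-correction shown above. A reader might also credit the laboratory and bone outcomes with a variance saving of a quarter to a half. That presumes a comparison of T2 values alone, which the article never states.

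Finally, the growth gain may be small. If z-scores track closely over three months, with r between 0.8 and 0.95, it is 1 to 4 percentage points of power. That is correct and sets the weight of the point.

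**Conclusion.** The point holds as a recommendation of modest size. For growth, the stated change analysis without the T0 value has a larger variance than baseline adjustment. The ANCOVA-to-change ratio is 0.85 to 0.95 for assumed correlations of 0.7 to 0.9, equivalent to 86% to 82% power in place of 80%, and about 81% at 0.95. The 80% is a reference level, since the trial was not sized on growth. The over-correction after a 0.2 SD imbalance is 0.06 SD or less over the same correlations. These figures rest on the assumed correlations and on equal SDs at T0 and T1. The advantage of ANCOVA is a large-sample result, and 63 per arm is ample for one extra term.

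For laboratory and bone outcomes, the T0 value is likewise not named, but the size of any gain cannot be fixed. The change analysis is not invalid: under randomisation it is unbiased on average, and the loss is one of efficiency and of conditional accuracy in the trial actually drawn.

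**What to change.** In Statistical analysis, state that T1 growth, as a z-score on the reference chosen for the child, is analysed by ANCOVA with the T0 z-score as covariate, alongside the covariates already named. Apply the same rule to the other continuous outcomes measured at T0: the LUS score at T1, and the laboratory and bone ultrasound values at T2. Pulmonary illness rate comes from a diary kept from T0 onward and has no evident T0 counterpart, so the rule does not reach it.

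Change may still be reported descriptively. Fixing the rule now also removes the option of choosing between change and adjusted analysis after baseline differences have been explored.

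The cost is one sentence of analysis text and one model term per outcome. No additional visit, measurement or participant is needed.
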